## Abstract

**Background:**

In the United States, young men who have sex with men (YMSM) and transgender women who have sex with men (YTWSM) bear a disproportionate burden of prevalent and incident HIV infections. Once diagnosed, many YMSM and YTWSM struggle to engage in HIV care, adhere to antiretroviral therapy (ART), and achieve viral suppression. Computer-based interventions, including those focused on behavior change, are recognized as effective tools for engaging youth.

**Objective:**

The purpose of the study described in this protocol is to evaluate the efficacy of Epic Allies, a theory-based mobile phone app that utilizes game mechanics and social networking features to improve engagement in HIV care, ART uptake, ART adherence, and viral suppression among HIV-positive YMSM and YTWSM. The study also qualitatively assesses intervention acceptability, perceived impact, and sustainability.

**Methods:**

This is a two-group, active-control randomized controlled trial of the Epic Allies app. YMSM and YTWSM aged 16 to 24 inclusive, with detectable HIV viral load are randomized 1:1 within strata of new to care (newly entered HIV medical care ≤12 months of baseline visit) or ART-nonadherent (first entered HIV medical care >12 months before baseline visit) to intervention or control conditions. The intervention condition addresses ART adherence barriers through medication reminders and adherence monitoring, tracking of select adherence-related behaviors (eg, alcohol and marijuana use), an interactive dashboard that displays the participant’s adherence-related behaviors and provides tailored feedback, encouragement messages from other users, daily HIV/ART educational articles, and gamification features (eg, mini-games, points, badges) to increase motivation for behavior change and app engagement. The control condition features weekly phone-based notifications to encourage participants to view educational information in the control app. Follow-up assessments are administered at 13, 26, and 39 weeks for each arm. The primary outcome measure is viral suppression. Secondary outcome measures include engagement in care, ART uptake, ART adherence, and psychosocial barriers to engagement in care and ART adherence, including psychological distress, stigma, and social support.

**Results:**

Baseline enrollment began in September 2015 and was completed in September 2016 (n=146), and assessment of intervention outcomes continued through August 2017. Results for primary and secondary outcome measures are expected to be reported in ClinicalTrials.gov by April 30, 2018.

**Conclusions:**

If successful, Epic Allies will represent a novel adherence intervention for a group disproportionately impacted by HIV in the United States. Adherent patients would require less frequent clinic visits and experience fewer HIV-related secondary infections, thereby reducing health care costs and HIV transmission. Epic Allies could easily be expanded and adopted for use among larger populations of YMSM and YTWSM, other HIV-positive populations, and for those diagnosed with other chronic diseases such as diabetes and hypertension.

**Trial Registration:**

ClinicalTrials.gov NCT02782130; https://clinicaltrials.gov/ct2/show/NCT02782130 (Archived by Webcite at http://www.webcitation.org/6yGODyerk)

## Introduction

### Background

Men who have sex with men (MSM) account for nearly two-thirds of all new HIV infections in the United States and young MSM (YMSM) are the only risk group experiencing an increase in HIV incidence [1-3]. Regional studies suggest that HIV prevalence among transgender women is among the highest of all risk groups, especially among transgender women of color, and African American transgender women in particular [4-6]. Although likely underestimated, HIV prevalence among young transgender women, including young transgender women who have sex with men (YTWSM), ranges from 4.5% to 15.9% [7]. Youth diagnosed with HIV must adjust to living with a highly stigmatized health condition that requires lifelong medical management. Due to structural, developmental, and psychosocial barriers, many youth struggle to enter medical care, initiate antiretroviral therapy (ART), adhere to ART, or achieve viral suppression (VS) [8,9]. For YMSM and YTWSM who may already be ostracized from families and friends because of their sexual identity, receiving an HIV diagnosis can lead to an increase in social isolation, as well as negative affective states such as depression and anxiety, which may create additional barriers to HIV treatment [10-13]. Interventions for YMSM and YTWSM that increase engagement in care, ART uptake, ART adherence, and VS are needed to maximize the individual and public health benefits of treatment [14].

Computer-based interventions (CBIs), particularly those delivered online, can address some of the barriers that HIV-positive youth face in engaging in traditional face-to-face interventions, such as stigma, lack of social support, time, and transportation [15,16]. A growing body of scientific literature demonstrates equivalent outcomes from in-person and CBIs across a range of health behaviors [17-27]. Youth in particular are highly receptive to CBIs and as a result, CBIs have been widely advocated in the fields of adolescent health education and prevention [21,22,28-33].

As of January 2017, 88% of US adults are online, 95% have a cell phone, and 77% have a smartphone [34,35]. Youth (ages 18-29 years) have the highest levels of smartphone ownership at 92% [35]. US lesbian, gay, bisexual, and transgender individuals under the age of 35 years have had consistently higher rates of smartphone ownership than their general population counterparts [36,37]. In addition to increased smartphone ownership, the use of mobile phone apps is on the rise [38].

Serious games (games designed to accomplish a purpose, such as influencing learning, civic engagement, or health behavior change) are increasingly being used to address behavioral and psychological factors that inhibit adherence to medical treatment regimens [39-41]. Such games are intended to be goal-oriented, immersive, challenging, and motivating [42]. Games designed to improve health can influence health attitudes and improve behavior change self-efficacy [43-46]. As a result, games are an ideal platform to engage youth in behavior change as they have the ability to attract and maintain attention, avoiding the development of boredom and attrition [42]. The ability to add “fun” into design and game play serves to enhance overall motivation.

Social networking sites are also extremely popular among young adults. As of July 2015, 90% of black and 95% of white youth aged between 18 and 29 years use social networking sites [47]. MSM and transgender women have high rates of social networking use [6], in part, because online venues often represent one of a limited number of venues for connecting with one another. Social networking has been used successfully to change behaviors, increase social support, and reduce social isolation in HIV prevention and care interventions [48,49].

Epic Allies was developed based on the information, motivation, and behavioral (IMB) skills model [50] to address the urgent need for interventions that improve engagement in care, ART uptake, and ART adherence among YMSM and YTWSM. The app was created using an iterative process with input from the target population at each stage of development to ensure acceptability, relevance, and appeal [16]. We anticipate that the gaming features will enhance motivation for behavior changes related to engagement in care and ART adherence. Furthermore, social networking features will increase motivation by providing users with a sense of community and social support. Funded by the National Institutes of Health, we worked with programmers and designers at Caktus Consulting Group, LLC to develop and test the Epic Allies prototype and found it to be acceptable among a sample of HIV-positive YMSM [16].

### Aims and Objectives

The aim of this paper is to describe the study protocol for the randomized controlled trial (RCT) of the Epic Allies intervention. The first objective of the study is to test the efficacy of the Epic Allies intervention among HIV-positive YMSM and YTWSM by conducting a two-arm RCT. The primary outcome measure is VS. Secondary outcomes include engagement in HIV care (ie, completion of HIV-related care clinic visit in last 3 months), ART uptake (ie, initiation of ART in the last 3 months), ART adherence (ie, >90% of doses taken in previous week), and psychosocial barriers to engagement in care and ART adherence such as psychological distress, stigma, and social support.

The second objective is to qualitatively assess intervention acceptability, perceived impact, and potential for long-term sustainability. In-depth interviews with a subset of intervention arm participants conducted after the intervention period will evaluate acceptability of Epic Allies and examine participants’ perspectives on the relationship between app use and study outcomes and potential for long-term sustainability of app use.

## Methods

### Trial Design

This study is a two-arm parallel RCT that will test the 26-week Epic Allies intervention against a control condition that includes weekly phone-based notifications to encourage participants to view educational information in the control app (Figure 1). Approximately 200 YMSM and YTWSM will be enrolled from 5 participating sites that provide HIV medical care for youth. Participants will be randomized 1:1 to intervention or control arms that are balanced by new to care (newly entered HIV medical care within 12 months of baseline visit) or ART-nonadherent status (first entered HIV medical care more than 12 months before baseline visit). Outcomes of interest will be measured at baseline, week 13 (during intervention phase), week 26 (end of intervention phase), and week 39 (postintervention phase). In-depth qualitative app satisfaction interviews will be conducted with approximately 20 intervention arm participants at the end of intervention use at week 26 to assess intervention experiences, acceptability, perceptions of associations between app use and study outcomes, and potential for long-term sustainability of using the app to support ART adherence.

### Ethics

The study protocol was approved by the institutional review boards (IRB) at the University of North Carolina at Chapel Hill and all participating study sites, including University of South Florida, Tampa, FL; Stroger Hospital of Cook County, Chicago, IL; Montefiore Medical Center, Bronx, NY; Tulane Medical Center, New Orleans, LA; and University of North Carolina Hospital, Chapel Hill, NC (also includes Regional AIDS Interfaith Network, Charlotte, NC). Individuals who express interest in the study will be required to provide signed informed consent before medical records are abstracted to confirm eligibility or study procedures are performed. The informed consent documents will describe all study procedures in detail. During the informed consent process, site study staff will go over the consent documents and answer any questions that may arise. A waiver of parental consent for individuals younger than 18 years has been obtained for all sites given that this is a minimal-risk study.

### Participants

Individuals participating in this study must meet the following eligibility criteria: (1) HIV-1 infected; (2) aged from 16 to 24 years; (3) assigned male sex at birth, of any gender identity, and self-reports a desire to engage or is engaging in sex with men; (4) at least one VL collected within the 12 weeks before the baseline visit, and the VL collected closest to the baseline visit is greater than the lower limit of detection for the site-specific assay used to test the specimen; (5) reliable daily access to an Android- or iOS-based mobile phone with a data plan; and (6) able to speak and read English. Self-reported eligibility criteria will be verified through an in-person screening with site study staff. Medical eligibility criteria will be verified through medical chart abstraction by site study staff. Individuals who cannot provide consent due to active substance use or psychological condition will be considered ineligible.

### Recruitment and Enrollment

Potential study participants will be identified through medical chart reviews and/or medical provider referrals at participating sites. Identified individuals will be informed of the nature of the study, the information to be collected, and the evaluations and assessments that are involved. For individuals interested in study participation, self-reported eligibility criteria will be verified. Before confirmation of medical eligibility criteria, a signed informed consent will be obtained. Individuals who provide informed consent and meet all study eligibility criteria will be enrolled in the study and complete a baseline computer-assisted self-interviewing (CASI) survey.

### Randomization

Study participants will be classified as either new to care (newly entered HIV medical care within the 12 months before the baseline visit) or ART nonadherent (first entered HIV medical care more than 12 months before the baseline visit). Randomization will occur in a 1:1 ratio within each of the 2 classification strata separately, with an equal number of participants assigned to the intervention and control arms. Due to rolling enrollment, block randomization will be used to help ensure balance within strata. Status as new to care vs nonadherent (eg, eligibility group) will be chosen as the primary stratum and randomized separately in blocks of 4 participants. Study statisticians will not be blinded to study arm assignment because they will be involved in data quality control and quality assurance.

### Incentives

The amount of participant compensation for study participation is determined separately by each site and approved by each site’s IRB. Participants will receive US $40 to $60 for completion of each RCT assessment at baseline, week 13, week 26, and week 39. Intervention arm participants who log on to the Epic Allies app 12 out of the first 14 days after the baseline visit will receive US $20 as a one-time sign-on bonus and those who log on at least once in each 30-day period will receive US $10 to help defray costs associated with smartphone data usage during that period. Participants in the intervention arm who are selected for and complete the in-depth qualitative interview will receive US $20 to $50.

### Intervention Theoretical Model and Features

The design of Epic Allies was informed by the IMB skills model, which conceptualizes health behavior change (eg, medication adherence) as a product of mediators, including information about the behavior, motivation to change, and the skills needed to achieve change [50]. Studies testing the IMB model of ART adherence support relationships between information, motivation, and behavioral skills and medication adherence [51-55]. Group- and individual-level IMB-based interventions improve ART adherence [56-59], though none have been designed specifically for YMSM and YTWSM. Epic Allies’ features (see Multimedia Appendix 1) address numerous elements of the IMB model (Figures 2-11). For example, the gaming features are designed to enhance sustained app use and motivate patterning new adherence behaviors [60]. The social networking features allow users to give and receive support, a relevant need for many YMSM and YTWSM who experience social isolation due to HIV-related stigma and homophobia [61-63].

### Intervention and Control Conditions

At baseline visit, participants assigned to the intervention arm will download and install Epic Allies, create a 4-digit app password, and receive a guided tour of the app by site study staff. Intervention arm participants will have full access to all features of Epic Allies during the 26-week intervention period. Participants assigned to the control group will download and install the Epic Allies control app (phone notification messages only), create a 4-digit app password, and be provided with instructions on using the app. During the 26-week trial, control participants will receive weekly phone notifications that inform users that new content is available and one brief informational article will be provided. Control group articles are a subset of Daily Dose articles focused on ART adherence and HIV disease self-management.

**Figure 1 figure1:**
[figure not shown]
Epic Allies study schema. CASI: computer-assisted self-interviewing.

**Figure 2 figure2:**
[figure not shown]
Medication reminder setup. ART: antiretroviral therapy.

**Figure 3 figure3:**
[figure not shown]
Profile.

**Figure 4 figure4:**
[figure not shown]
Profile: Customizable avatar.

**Figure 5 figure5:**
[figure not shown]
Profile: Readiness badge.

**Figure 6 figure6:**
[figure not shown]
Health Center: Visual representation of adherence.

**Figure 7 figure7:**
[figure not shown]
Health Center: Weekly tailored feedback.

**Figure 8 figure8:**
[figure not shown]
Ally interactions.

**Figure 9 figure9:**
[figure not shown]
The Daily Dose.

**Figure 10 figure10:**
[figure not shown]
Mini-games: Social game leaderboard.

**Figure 11 figure11:**
[figure not shown]
Mini-games: Mind Mine.

### Data Collection Study Objective 1: Efficacy

Baseline, week 13, week 26, and week 39 assessments will be conducted in person. At each time point, participants will complete a CASI survey. Clinical data will include data collected via chart abstraction and/or laboratory values (VL only). If a participant does not have a VL value recorded in their chart in the 6-week window before the study visit, VL testing will be conducted on the day of the study visit as part of standard of care (ie, participant is scheduled for a medical care visit that includes VL testing) or by the study (ie, the study visit does not coincide with a medical care visit with VL testing). Table 1 lists primary and secondary outcomes and the source, collection points, and a description of each measure.

App usage data will be transmitted from the participant’s smartphone to a secure server any time the participant is connected to the Internet via broadband or Wi-Fi. App data metrics include log-ins/log-outs, use of app features, and app progress.

### Data Collection Study Objective 2: Acceptability

In-depth qualitative app satisfaction interviews will be conducted via Skype with approximately 20 intervention arm participants at the end of the intervention. We will attempt to enroll equal numbers of participants into one of four cells in Table 2 based on their ART status at study entry and app usage during the intervention. As each participant finishes the 26-week intervention period, they will be asked if they are willing to participate in the in-depth app qualitative satisfaction interview. Once a given care-usage cell has reached its quota, that cell will be “closed,” and interviews will be offered to only those participants who fall within the remaining open cells.

The in-depth qualitative app satisfaction interview will last between 45 and 60 min and will be recorded with the participant’s consent. Participants who prefer can opt to use video during the interview, but there will be no video recording. All interviews will be conducted by one of 3 trained qualitative interviewers from the study team using a semistructured interview guide. Following each interview, the recording will be transcribed by Verbal Ink (a division of Ubiqus, Los Angeles, California), checked for accuracy by study staff, and uploaded to the UNC-CH secure server. The transcripts of the first three interviews will be reviewed by the study team to assess for quality and content before completing the remaining interviews.

**Table 1 table1:** Primary and secondary outcomes. “X” indicates that this outcome was assessed at the time point indicated in the column above. VS: viral suppression. VL: viral load. CASI: computer-assisted self-interviewing. ART: antiretroviral therapy.

Outcome		Source	13 weeks	26 weeks	39 weeks	Description
**Primary study outcomes**						
	VS defined as VL below the lower limit of detection in the 6-week window before the scheduled study visits	Chart review (any value in 6-week window before scheduled visit) OR laboratory value collected at study visit	X	X		<40 copies/mL or lower limit of detection for site-specific assay used to test the specimen
**Secondary study outcomes**						
	VL suppression defined as VL below the lower limit of detection in the 6-week window before the scheduled study visits	Chart review (any value in 6-week window before scheduled visit) OR laboratory value collected at study visit			X	<40 copies/mL or lower limit of detection for site-specific assay used to test the specimen
	Engagement in care	CASI survey	X	X	X	Completion of HIV-related care clinic visit in last 3 months
	ART uptake (for participants not on ART)	CASI survey	X	X	X	“Are you currently taking medication to treat your HIV (Y/N)?”
	ART adherence^a^ (for participants on ART)	CASI survey	X	X	X	(1) “How many times during the day has your doctor told you to take a dose of medicine (pills or other medicines) to treat your HIV?” and (2) “Thinking about the last 7 days, how many times did you miss taking a dose of pills?”[64]

^a^Outcome of >90% adherence is comprised 2 components (1) is the denominator, indicating the frequency of doses prescribed (multiplied x7 to represent total weekly doses); (2) is the numerator, indicating the number of times, total, a dose was missed.

**Table 2 table2:** In-depth qualitative app satisfaction interview enrollment.

Antiretroviral therapy (ART) experience at entry		New to care	ART nonadherent	Total

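### Table 1 footnote a makes missed doses the numerator of the >90% adherence outcome, which contradicts the Aims, where the outcome is doses taken

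*Protocol article*

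**What the plan says.** In Aims and Objectives the outcome is given as "ART adherence (ie, >90% of doses taken in previous week". The threshold there applies to doses taken.

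Table 1 bases the outcome on two self-reported survey items, asked at weeks 13, 26 and 39 of participants who are on ART. The first asks "How many times during the day has your doctor told you to take a dose of medicine". The second asks "Thinking about the last 7 days, how many times did you miss taking a dose of pills".

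Footnote a then says how the two answers become the outcome. It opens with "Outcome of >90% adherence is comprised 2 components". It assigns the first item its role: "1) is the denominator, indicating the frequency of doses prescribed (multiplied x7 to represent total weekly doses". It assigns the second item the other role: "2) is the numerator, indicating the number of times, total, a dose was missed". The footnote does not subtract the ratio from 1, and it does not convert missed doses into taken doses. No other part of the article says how the outcome is calculated.

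**The concern.** A numerator of missed doses over a denominator of prescribed doses gives the share of doses missed. Applying a >90% cut-off to that share selects people who took almost nothing, whereas the Aims require the cut-off to select people who took almost everything. The two definitions cannot both be followed.

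Adherence is the behaviour that the app is built to change, so readers will want to interpret this outcome next to viral suppression. Anyone who programs it from Table 1, or tries to reproduce it, would take the formula from the footnote, because the Aims give only the threshold. Followed to the letter, the footnote produces a variable that does not measure the stated outcome.

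**Working it through.** **Inputs.** Let k be the prescribed doses per day (first survey item) and m the doses missed in the last 7 days (second item). Weekly prescribed doses are 7k, as in footnote a. The threshold is >90% in both places. The article does not give participants' dosing frequencies, so k = 1, 2 and 3 are illustrative. The article reports no adherence result, so there is no published figure to reproduce, only the rule to test.

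**Two rules.**
- Footnote a as written: m / (7k) > 0.90
- Aims and Objectives: (7k − m) / (7k) > 0.90, which is the same as 1 − m/(7k) > 0.90

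**Who meets each rule.**

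| Doses per day | Weekly doses | Footnote as written: missed doses that pass | Aims: missed doses that pass |
|---|---|---|---|
| 1 | 7 | 7 only (6/7 = 85.7% does not pass) | 0 only (1 missed: 6/7 = 85.7%) |
| 2 | 14 | 13 or 14 (13/14 = 92.9%; 12/14 = 85.7% does not pass) | 0 or 1 (1 missed: 13/14 = 92.9%; 2 missed: 12/14 = 85.7%) |
| 3 | 21 | 19, 20 or 21 (19/21 = 90.5%; 18/21 = 85.7% does not pass) | 0, 1 or 2 (2 missed: 19/21 = 90.5%; 3 missed: 18/21 = 85.7%) |

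**Extremes.** Under the footnote, a once-daily participant with no missed dose scores 0/7 = 0% and is classed as not adherent. One who missed every dose scores 7/7 = 100% and is classed as adherent. Under the Aims, the same two people score 100% and 0%.

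**Are the two rules mirror images?** No. Once daily, anyone who missed 1 to 6 doses fails both. Twice daily, anyone who missed 2 to 12 doses fails both. The literal rule is therefore an indicator of near-total non-adherence. It is not the complement of the intended outcome.

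**Does it reach the primary analysis?** No. Sample Size and Power Estimates rests on viral suppression, and Table 1 takes viral suppression from chart or laboratory values. Neither uses the adherence items.

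**The case against.** The strongest reply is that this is a drafting slip with an obvious resolution. The footnote itself calls the outcome adherence, and the Aims state the direction outright. An analyst who read both would compute one minus the ratio without hesitation. The outcome is one of several secondary outcomes, none singled out as key, and Limitations already warns that self-reported outcomes may be misclassified.

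Most of that stands. The intended direction is not in doubt and the primary result is not at risk. It does not remove the point. The footnote does more than leave a step unstated: it names a numerator, and that numerator gives the wrong quantity. A general caution about self-report does not cover a formula that points the wrong way.

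A reader might infer more than the article supports:

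- **That non-adherers were, or will be, counted as successes.** The article shows only the written rule. It shows neither code nor adherence results.
- **That the treatment effect would simply reverse.** The two rules are not complements, as shown above. The literal rule would give a different variable, and the planned effect would not come back with its sign changed.
- **That the cut-off misclassifies people by regimen**, because one missed dose fails once daily (85.7%) and passes twice daily (92.9%). One dose in 7 and one in 14 are different proportions of what was prescribed, and each person is classed correctly against >90% of doses taken. The equivalent lapse twice daily, 2 of 14, also gives 85.7% and also fails. This coarseness comes from counting whole doses over 7 days and is not an error. Both arms share the rule, and allocation is randomized, so nothing suggests a systematic difference between arms.
- **That a count model should become the main analysis.** Quantitative Data Analysis allows count models but does not assign one to adherence. A fixed threshold is a legitimate choice, and a count model with an offset has a drawback of its own, since missed doses are capped at the number prescribed.

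**Conclusion.** The point holds as a contradiction between two statements of the same secondary outcome. Footnote a describes the proportion missed and the Aims describe the proportion taken. Taken literally, the footnote scores perfect adherence as 0% and admits only near-total non-adherence: 7 of 7 doses once daily, or 13 or 14 of 14 twice daily. This follows from the footnote's own terms by arithmetic and needs no assumption beyond the dosing frequency used to illustrate it.

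The footnote should be corrected because it is the only computation on record and gives a wrong result if followed. The consequence is limited to this outcome and to whether the derivation code matches the Aims, which the article cannot show. The primary analysis and the power statement are unaffected.

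**What to change.** Restate footnote a so that it agrees with the Aims: adherence = 1 − missed / (7 × prescribed daily doses), with the outcome met when this exceeds 0.90. Equivalently, define the numerator as prescribed weekly doses minus missed doses.

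Then check that the derivation code uses this form. Two test records are enough: once daily with no missed dose must be classed adherent, and once daily with 7 missed must not. If the code followed the literal footnote, rerun the adherence analyses.

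When reporting, it may help to note that for once-daily regimens >90% amounts to no missed dose in 7 days. This is a description of the measure and needs no change to it. The prespecified binary outcome can stay as it is.

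The cost is one corrected sentence and a short code check. Both survey items are already in the planned data collection, so no new data are needed.
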